### Statistical considerations

For sample size assessment, a pilot study of 60 patients was conducted in which we observed that successful intubation could be achieved in the first attempt in 100% (30/30) of patients in group B (TAS) but was achieved in 90% (27/30) of group A (PIS). To detect a similar difference between the success of intubation (100 versus 90%) with a statistical power of 80% and 95% confidence interval and equal distribution of patients in both the groups, a total sample size of 154 was estimated for the present study using the open source browser-based calculator OpenEpi [16]. However, in light of the stratification used for randomization the final sample size of 158 shall be used with equal distribution. All statistical evaluations will be made at a significance level of 0.05 (two-sided). A two-sided, 95% confidence interval will be calculated for the mean difference between the treatment groups. The data will be analyzed on an intention-to-treat basis. No imputations will be used for any missing data. The primary efficacy variable of success/failure between the two groups will be analyzed using the chi square/Fisher’s exact test, whichever will be applicable. Binary logistic regression will also be used on the whole dataset to identify predictors of success/failure of intubation. For evaluation of intubation times and the intubation difficulty score, analysis of variance (ANOVA) will be used for comparison between both treatment groups. The intubation difficulty scale (IDS) will also be transformed into an ordinal variable (0, 0 to 5, >5) and multinomial logistic regression will be used to evaluate for possible predictors of a difficult intubation.

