**Figure 4 F4:**
[figure not shown]
**Stylets used in the intervention arms. (a)** Conventional Portex™ intubation stylet used in group A patients. **(b)** Truflex™ articulating stylet with stopper used in group B patients.

Primary efficacy endpoints will be successful or failed tracheal intubation in the first attempt, total intubation time and the intubation difficulty score. An attempt will be counted if the laryngoscope or the ETT needs to be removed for re-oxygenation (drop in oxygen saturation by 5%) or for reshaping of the ETT. The total intubation time will be the sum of the glotticoscopy time (from introduction of the videolaryngoscope blade between the teeth to the best laryngeal view) and the ETT negotiation time (from receiving the styleted ETT in laryngoscopist’s hand to passage of the black line just beyond the vocal cord). Secondary efficacy endpoints will be overall user satisfaction graded from 1 to 10 (1 = very poor, 10 = excellent), Cormack and Lehane’s grading, glotticoscopy time and ETT negotiation time and total number of intubation attempts with a maximum of three attempts, after which an alternative technique will be used. Safety endpoints assessed will be dental and airway trauma (present or absent), hemodynamic disturbances (blood pressure and pulse rate would be recorded before intubation, 1 minute and 5 minutes post-intubation; ≥20% change from the baseline value will be considered clinically important), arrhythmias (absent or present; type if present), or cardiac arrest.

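### A patient in whom all three attempts fail has no total intubation time as defined, and the no-imputation rule then removes that patient from a primary comparison described as intention-to-treat

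*Protocol article*

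**What the plan says.** The endpoint definitions are in the Methods section of the protocol article: "Primary efficacy endpoints will be successful or failed tracheal intubation in the first attempt, total intubation time and the intubation difficulty score". Total intubation time is the sum of two intervals. The second, the tube negotiation time, runs "from receiving the styleted ETT in laryngoscopist’s hand to passage of the black line just beyond the vocal cord". The number of attempts is a secondary endpoint, recorded "with a maximum of three attempts, after which an alternative technique will be used".

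The section Statistical considerations sets the analysis: "The data will be analyzed on an intention-to-treat basis. No imputations will be used for any missing data". For the times it says: "For evaluation of intubation times and the intubation difficulty score, analysis of variance (ANOVA) will be used for comparison between both treatment groups". It also promises a 95% confidence interval for the mean difference between the groups.

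The article gives no censoring time, substitute value or rank for the time of a patient in whom the assigned stylet fails.

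**The concern.** Put together, these statements leave one kind of patient without a value. If three attempts fail and another technique takes over, the event that stops the clock has not occurred with the styleted tube. The total time is then undefined. Under a rule that bars imputation of any missing data, the patient cannot enter the ANOVA or the confidence interval for the mean difference. The tube negotiation time, a secondary endpoint, has the same gap.

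The loss depends on the outcome: the patients removed are those in whom the device performed worst. An analysis of the remaining patients compares successes with successes, not the groups as randomised, and it shortens the observed mean of whichever arm has more complete failures. A shorter intubation time is the first benefit named in the trial's hypothesis (Background), so the point touches a central claim. If the rule is settled only once the failures are known, the choice will be made with the results in view.

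**Working it through.** **Inputs from the protocol article.** Final sample 158 with equal allocation, so 158/2 = 79 per arm. Pilot first-attempt success 30/30 (100%) with Truflex and 27/30 (90%) with Portex. Two-sided level 0.05, power 80%. At most three attempts.

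**Inputs not in the article, assumed here.** The share q of Portex patients not intubated within three attempts; a mean time of 30 s and SD of 15 s; a failure counted as 120 to 300 s.

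**The plan's own figure.** The pooled-variance formula 2 × 0.95 × 0.05 × (1.960 + 0.842)² / 0.10² gives 74.6, so 75 per arm and 150 in total, within 3% of the stated 154. Entering 100% as 99.9% (an assumption about how the calculator was used) gives 76.8, so 77 per arm and exactly 154. The sample size rests on first-attempt success and does not change with this point.

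**How many patients could lose their time.** Only failure of all three attempts removes a time; a second- or third-attempt success reaches the end of the interval. The first-attempt failure rate is therefore only an upper bound. If it is 10% and each later attempt fails with probability r, then q = 0.10 × r². The expected number is 79q, the chance of at least one is 1 − (1 − q)^79, and the expected fall in the Portex mean is q × (T − 30), where T is the time a failure would count as.

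| q | Expected of 79 | Chance of at least one | Fall, T = 120 s | Fall, T = 180 s |
|---|---|---|---|---|
| 0.1% (r = 0.1) | 0.08 | 8% | 0.1 s | 0.15 s |
| 1% | 0.8 | 55% | 0.9 s | 1.5 s |
| 2.5% (r = 0.5) | 2.0 | 86% | 2.25 s | 3.75 s |
| 10% (r = 1, upper bound) | 7.9 | >99.9% | 9 s | 15 s |

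**Effect of one lost patient.** With 78 successes averaging 30 s and one failure at T, the mean over all 79 exceeds the mean of the successes by (T − 30)/79:
- T = 120 s: 90/79 = 1.1 s
- T = 180 s: 150/79 = 1.9 s
- T = 300 s: 270/79 = 3.4 s

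**Effect on the test.** Simulation with 79 per arm, identical time distributions in both arms (mean 30 s, SD 15 s), the slowest k Portex patients dropped, two-group ANOVA (equivalent to the t-test), 40,000 trials per setting:

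| k dropped | False-positive rate, normal times | False-positive rate, lognormal times |
|---|---|---|
| 0 | 5.0% | 5.0% |
| 1 | 5.6% | 6.6% |
| 2 | 7.0% | 9.3% |
| 4 | 11.5% | 17.5% |

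The excess favours Portex. With four dropped and lognormal times, Portex looks 2.2 s faster on average, and a false result in favour of Truflex occurs in only 0.3% of trials.

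**The case against.** The strongest reply has four parts.

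**The problem may hardly arise.** The 90% and 100% are first-attempt rates. If attempts failed independently at 10% each, about 0.08 Portex patients of 79 would be affected. This stands. A reader might infer that a tenth of the Portex arm loses its time, but nothing in the article supports that; 7.9 patients is the extreme in which every first-attempt failure also fails twice more. Nor can one infer that losses occur only with Portex: 30 of 30 successes leaves a one-sided 95% upper limit of 1 − 0.05^(1/30) = 9.5% for Truflex first-attempt failure.

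**Failures are counted elsewhere.** They enter first-attempt success, which the sample size rests on, and the number of attempts. This also stands, so the intention-to-treat statement is not undermined for the trial as a whole. It does not repair the time comparison, which is listed as primary too.

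**The bias runs against the sponsor's hypothesis.** On the planning rates this is right. A reader might suspect that the rule manufactures a Truflex advantage; it would do so only if Truflex had more complete failures. A bias that conceals a real benefit is still a bias.

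**The text is silent rather than contradictory.** The article does not label a failed intubation as missing data, and the clock could be meant to run until a tube passes by any technique. Details of this kind often go into an analysis plan. This stands in part. But the interval is defined from receipt of the styleted tube, and the ban covers any missing data without exception. Followed as printed, it drops these patients; if another reading is meant, it needs to be stated.

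The simulation also has limits: it lets only Portex's slowest patients fail although the time distributions are identical. In a similar run that dropped the slowest 5% in both arms, the false-positive rate was 5.1% with no bias. Large error rates should therefore not be quoted as expected behaviour of this trial.

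**Conclusion.** The concern holds for total intubation time and, through it, the tube negotiation time. As written, the plan makes the comparison conditional on intubation within three attempts, despite the intention-to-treat statement. It does not touch first-attempt success or patients intubated on a second or third attempt.

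The direction is predictable: the arm with more complete failures looks faster, which on the planning rates is Portex. The size cannot be fixed from the article. Under the assumed times, one lost patient is nearly harmless to the error rate (about 6%), two give roughly 7 to 9%, and four give roughly 12 to 18%, depending on how skewed the times are. This should be fixed, but it is not a fatal flaw.

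**What to change.** State that failure with the assigned stylet is an observed outcome, not missing data. Record for every patient the time to tube passage or to abandonment of the assigned stylet, whichever comes first. Keep every randomised patient in the total-time analysis with that value, noting that for failures it is a lower bound. Because a lower bound still understates a failure, add a sensitivity analysis that ranks failures worst, using a Wilcoxon test stratified by ADA stratum. Limit the no-imputation rule to values missing for reasons unrelated to the outcome.

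The cost is a few sentences of wording, one extra recorded time in a few patients and one extra analysis. The sample size, the procedures and the cap on attempts are unchanged. Trial status reports 11 patients recruited at submission, so at that point the rule could have been set before most of the data existed.

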**Methods:**

One hundred and fifty four patients between 18 and 60 years of age belonging to either sex undergoing tracheal intubation under uniform general anesthetic technique will be randomly divided into Portex™ malleable stylet group and Truflex™ articulating stylet group. The primary efficacy variable of success/failure between the two groups will be analyzed using the chi square test. For comparison of intubation times and the Intubation Difficulty Score, ANOVA will be used. Primary efficacy endpoint results will be successful or failed tracheal intubation in the first attempt, total intubation time and the intubation difficulty score. Secondary efficacy endpoints will be overall user satisfaction graded from 1 to 10 (1 = very poor, 10 = excellent), Cormack and Lehane’s grading, glotticoscopy time and ETT negotiation time and total number of intubation attempts. Result of safety endpoints will include dental and airway trauma, hemodynamic disturbances, arrhythmias or cardiac arrest.

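### The primary test is chi-square in the abstract but chi-square or Fisher in the methods; the two can disagree at 4 or 5 v 0 failures, and naming one exact test would settle it and add power

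*Protocol article*

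**What the plan says.** The Methods paragraph of the abstract gives a single test: "The primary efficacy variable of success/failure between the two groups will be analyzed using the chi square test". Statistical considerations, in the body of the article, offers chi-square or Fisher's "exact test, whichever will be applicable", and does not say what makes either one applicable. Both are current text and concern the same endpoint, the one that sizes the trial.

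The design inputs are in Statistical considerations. The pilot gave 30/30 first-attempt successes with TAS and 27/30 with PIS. The target is worded "To detect a similar difference between the success of intubation (100 versus 90"%), "with a statistical power of 80% and 95% confidence interval". The calculated total is 154 and the final total is 158 in equal groups, so 79 per arm. The test level is also fixed there: "All statistical evaluations will be made at a significance level of 0.05 (two-sided").

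**The concern.** With a success rate near 100% in one arm, the primary comparison rests on a handful of failures. That is where an uncorrected chi-square and Fisher's exact test differ most, because Fisher is conservative with few events. If the two straddle 0.05, the conclusion on this endpoint depends on whether a reader follows the abstract or the body, and on how the body's clause is understood. The fallback to Fisher also gives up power that another valid exact test would keep.

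**Working it through.** **1. The plan's own figure.** The pooled-variance formula is n per arm = 2p̄(1−p̄)(1.960+0.842)²/d².
- With 100% v 90%: p̄=0.95, d=0.10, n = 2×0.0475×7.849/0.01 = 74.6. Rounded up to 75, the total is 150.
- With 100% entered as 99.9% (an assumption about how the calculator was used): p̄=0.9495, d=0.099, n=76.8. Rounded up to 77, the total is 154, as stated.

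**2. P-values at n=79 per arm, k PIS failures and 0 TAS failures.**
- Uncorrected chi-square: X² = 158k/(158−k). For k=4, 632/154=4.10; for k=5, 790/153=5.16; for k=8, 1264/150=8.43.
- Two-sided Fisher: p = 2×C(79,k)/C(158,k).
- The smallest expected count is half the total number of failures, k/2.

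| PIS v TAS failures | Smallest expected count | Chi-square p | Fisher p | Same verdict? |
|---|---|---|---|---|
| 3 v 0 | 1.5 | 0.080 | 0.245 | yes, neither significant |
| 4 v 0 | 2.0 | 0.043 | 0.120 | no |
| 5 v 0 | 2.5 | 0.023 | 0.059 | no |
| 6 v 0 | 3.0 | 0.0125 | 0.028 | yes, both significant |
| 8 v 0 | 4.0 | 0.0037 | 0.0065 | yes, both significant |

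The expected number of PIS failures is 79×0.10=7.9, so 8 v 0 is the planned result. With some TAS failures the tests also disagree at 7 v 1 (0.030 v 0.063), 8 v 2 (0.0499 v 0.098), 9 v 2 (0.029 v 0.056) and 10 v 3 (0.043 v 0.079).

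**3. How likely disagreement is.** With PIS failures binomial (79, 0.10) and no TAS failures:
- 0 to 3 failures: 3.8%, neither test rejects.
- 4 or 5 failures: 14.8%, opposite verdicts.
- 6 or more failures: 81.4%, both reject.

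If TAS fails in 1% to 3% of patients (assumption), disagreement has probability 15% to 17%. The 90% rests on 27/30, with an exact 95% interval of about 73% to 98%. With TAS kept at 100%, disagreement has probability 27% at 92% PIS success, 33% at 93% and 37% at 94%.

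**4. Power under 100% v 90% at 79 per arm.**
- Uncorrected chi-square rejects from 4 v 0: 96.2%.
- Fisher rejects from 6 v 0: 81.4%.
- Boschloo's two-sided test gives p=0.094 at 4 v 0 and p=0.046 at 5 v 0. It rejects from 5 v 0: 81.4% + P(5 failures) 9.3% = 90.7%, or 90.6% before rounding.

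Fisher's true type I error is 1.6% when both arms fail at 5%. Boschloo takes its p-value as the maximum over the common failure rate, so the 5% level is held by construction.

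**5. What chi-square means.** A continuity correction changes the picture: at 5 v 0 the Yates p-value is 0.069 against 0.023 without it. Under 10% v 0% failures, Yates and Fisher never disagree.

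**The case against.** The body's clause is common shorthand for using Fisher when an expected count falls below 5. On that reading 4 v 0 and 5 v 0 both go to Fisher and no choice is left. With equal arms the smallest expected count depends only on the total number of failures, so the treatment difference cannot steer the choice. The procedure also performs adequately. Power is 81.4% under the design, and type I error is 2.9%, 5.0% and 5.1% at common failure rates of 5%, 8% and 10%. An abstract condenses, and the exact switching threshold is a detail an article may leave to fuller documents.

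Most of this stands. Two parts do not dispose of the point. The convention is not written down, and at 4 v 0 and 5 v 0 it gives the opposite answer to the abstract's chi-square test if that is uncorrected. And under 100% v 90% the convention would select Fisher about 74% of the time and chi-square otherwise, so the test is known only once the failures are counted.

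A reader might infer that the tests conflict at the failure counts the trial expects. They do not: at 6, 7 or 8 v 0 both are significant. Nor do the figures show that the trial is underpowered if Fisher is used at the final size of 158.

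**Conclusion.** Minor. The two places name different procedures for the same endpoint, and the choice changes the verdict in about 15% of trials under the design's own rates, at PIS failure rates of 5% to 6% rather than the planned 10%. Fisher alone meets the stated 80% power at 158 patients (81.4%; at 154 it would be 79.4%), so nothing in the sample size needs repair on this account. The gain is a primary result that does not depend on which sentence is followed, plus about 9 points of power (81.4% to 90.6%) at no cost in patients.

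This rests on 79 analysed per arm, no TAS failures, 10% PIS failures, an uncorrected chi-square, and the expected-count convention as the meaning of the open clause. The power comparison would shrink if TAS failures occur.

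**What to change.** Name one prespecified primary test for first-attempt success in the abstract and in Statistical considerations, and delete the clause that leaves the choice open. Boschloo's two-sided unconditional exact test is the suggested choice. State the two-sided convention and the software, since definitions can differ if the analysed arms are unequal. Report Fisher's test as a sensitivity analysis.

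The alternative is an exact Cochran-Mantel-Haenszel test by the anticipated difficult airway (ADA) stratum. It matches the stratified randomisation, but no power gain has been shown for it here. If the team prefers chi-square, it should state whether a continuity correction is used.

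The cost is one sentence in each place. The downside is that Boschloo's test is less familiar to clinical readers. Trial status reports 11 patients recruited at submission, so at that stage the change could be made before outcomes could influence it.

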The present trial (ISRCTN57679531) aims at utilizing the Truflex™ articulating stylet (TAS) (Truphatek) as a dynamic aid to tailor the ETT shape in its very first attempt as per the videolaryngoscope blade design (Figure 2) and the patient’s oropharyngeal anatomy. We hypothesize that a pre-loaded ETT over the TAS will not only shorten the D-blade C-Mac™ videolaryngoscope-aided intubation time, but will also attenuate the hemodynamic response and reduce the possibility of soft-tissue trauma, both in patients with normal anatomy and in those whose anatomy makes access more difficult, compared to non-dynamic PIS-aided tracheal intubation.

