## Methods

The study protocol has been approved by the Ethical Issues Committee, Khoula hospital. The current study is an interventional, single-blinded, parallel assignment, randomized controlled trial. The aim of the study is to compare the conventional rigid Portex™ stylet with the Truflex™ articulating stylet as an intubation guide during videolaryngoscopy. Stratified block randomization with variable block sizes will be done (Figure 3). The freeware Random Allocation software of Mahmood Saghaei will be used for generating randomization sequences [15]. Stratification will be based on anticipated difficulty in intubation based on the anticipated difficulty airway (ADA) score (Table 1). Sealed opaque envelopes will be used for allocation concealment with sequential numbering within each stratum. For randomization the envelopes will be opened only after transporting the patient to the operating theater, thus, maintaining allocation concealment and only one envelope can be opened per patient.

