**Figure 3 F3:**
[figure not shown]
**Scheme of stratified randomization.** After appropriate exclusions all eligible patients will undergo airway assessment with the ADA score and stratified into easy and difficult airway strata, and will then be randomized into the two treatment groups. ADA, anticipated difficult airway; PIS, Portex™ intubation stylet; TAS, Truflex™ articulating stylet.

**Table 1 T1:** **Anticipated difficult airway (ADA) score**^*****^

**Airway factors**	**Score**		
	**0**	**1**	**2**
**Mallampati classification**	Class I	Class II	Class III to IV
**Thyromental distance, cm**	>6.5	6.0 to 6.5	<6.0
**Head and neck movement, degrees**	>90	90	<90
**Body mass index, kg/m**^**2**^	<25	≥25	NA
**Buck teeth**	No	Mild	Severe
**Inter-incisor gap, cm**	>5.0	4.0 to 5.0	<4.0

^*^Easy airway strata: ADA score ≤6; difficult airway strata: ADA score >6; NA- Not applicable.

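### Randomisation is stratified by ADA score, but the stated between-group tests leave the stratum out, so the comparisons of time and IDS are conservative if the stratum is prognostic

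*Protocol article*

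**What the plan says.** **Allocation.** Methods states that "Stratified block randomization with variable block sizes will be done" and that "Stratification will be based on anticipated difficulty in intubation based on the anticipated difficulty airway (ADA) score". The footnote to Table 1 sets two levels: "Easy airway strata: ADA score ≤6; difficult airway strata: ADA score >6".

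**Endpoints.** The endpoint paragraph of Methods says: "Primary efficacy endpoints will be successful or failed tracheal intubation in the first attempt, total intubation time and the intubation difficulty score".

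**Tests.** Statistical considerations fixes the between-group comparisons. For the binary endpoint: "The primary efficacy variable of success/failure between the two groups will be analyzed using the chi square/Fisher’s exact test, whichever will be applicable". For times and IDS: "analysis of variance (ANOVA) will be used for comparison between both treatment groups". Neither sentence mentions the stratum. The same section raises the total from 154 to 158 on account of the stratification. It also plans regressions whose covariates are not named: "Binary logistic regression will also be used on the whole dataset to identify predictors of success/failure of intubation", and a multinomial model for categorised IDS.

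**Hypothesis.** The last paragraph of the Background expects the articulating stylet to shorten intubation, blunt the haemodynamic response and reduce soft-tissue trauma, "both in patients with normal anatomy and in those whose anatomy makes access more difficult".

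**The concern.** One stratifies on anticipated difficulty because it is expected to predict failure, time and difficulty score. Stratified allocation balances the arms on that factor, so the treatment difference varies less from trial to trial. An analysis without the factor still counts the easy–difficult gap as residual error, and the reported standard error is then larger than the true one. Confidence intervals come out too wide and the test rejects less often than its nominal 5%. The plan recognised the stratification when it set the sample size, but did not carry it into the tests.

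There is also a question of interpretation. The hypothesis names both kinds of anatomy, while the stated comparisons are pooled. A pooled result can be driven by one stratum and cannot by itself support a statement about difficult airways.

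**Working it through.** **Inputs from the documents.** Success 100% versus 90%; 80% power; two-sided 0.05; 1:1; 154 calculated, 158 final (79 per arm); two ADA strata.

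**Assumed, because the documents give no figure.** The R² of the stratum for time or IDS, the share of patients in the difficult stratum, and how failures split between strata.

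**1. The plan's own sample size.** With the pooled-variance formula, n per arm = (1.960 + 0.842)² × 2p̄(1 − p̄)/(p₁ − p₂)². With p̄ = 0.95 and a difference of 0.10 this gives 74.6, so 75 per arm and 150 in total, within 3% of 154. Entering 99.9% for 100% gives 76.8, so 77 per arm and exactly 154. The figure reproduces, and it contains no stratum term.

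**2. Time and IDS.** With arms balanced within strata, the true variance of the difference in means is proportional to 1 − R², while the unadjusted ANOVA reports it as if R² were 0. Let r = 1/√(1 − R²). Then:

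- standard error ratio, unadjusted to true = r
- type I error of the unadjusted test = 2Φ(−1.960r)
- adjusted power, where the ordinary formula puts unadjusted power at 80%, = Φ(2.802r − 1.960)

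| R² (assumed) | SE too large by | Type I error | Adjusted power (unadjusted 80%) |
|---|---|---|---|
| 0.02 | 1% | 4.8% | 80.8% |
| 0.05 | 3% | 4.4% | 82.0% |
| 0.10 | 5% | 3.9% | 84.0% |
| 0.20 | 12% | 2.8% | 87.9% |
| 0.30 | 20% | 1.9% | 91.8% |

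The ordinary formula ignores that stratified allocation already reduces the true variance. Allowing for it, the unadjusted test's realised power is Φ(0.842r), or 80.2% to 84.3% over this range, and the gap to the adjusted analysis is 0.5 to 7.5 points. If instead the adjusted analysis is set at 80%, unadjusted power is Φ(2.802 − 1.960r), or 79.4% down to 67.7%, and the gap is again about 1–12 points. Simulated trials with 79 per arm agree: at R² = 0.20 (equal strata), 72.7% unadjusted against 79.8% adjusted, with unadjusted type I error 2.5%.

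**3. First-attempt success.** At the design rates about 7.9 failures are expected, all in the rigid-stylet arm, so about 4 per arm under the null. That is below the usual limit of 5, and in about 74% of trials the plan's choice would fall to Fisher. Fisher needs 6 failures against 0 (5 against 0 gives p = 0.059), and P(X ≥ 6) for Binomial(79, 0.10) is 81.4%. Exact enumeration against a stratified exact test gives:

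| Difficult share | Failures in that stratum | Pooled Fisher | Stratified exact |
|---|---|---|---|
| any of 20%, 30%, 50% | in proportion to size | 81.4% | 81.4% |
| 20% | 50% | 82.2% | 82.5% |
| 20% | 70% | 83.9% | 85.7% |
| 20% | 80% | 85.1% | 88.5% |
| 20% | 90% | 86.7% | 92.0% |
| 30% | 50% | 81.7% | 81.9% |
| 30% | 70% | 82.6% | 84.2% |
| 30% | 80% | 83.2% | 86.5% |
| 30% | 90% | 84.1% | 89.7% |
| 50% | 80% | 81.9% | 81.9% |

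Where the uncorrected chi-square is used, it and the Cochran-Mantel-Haenszel (CMH) test have the same power, 96–98%, at the design rates. With the articulating stylet at 98% rather than 100%, chi-square has 60–62% and CMH 57–66%, a change of −3 to +5 points.

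**4. The difficult stratum alone.** Suppose the same 100% versus 90% holds there and the stratum contains 10%, 20%, 30% or 50% of patients (8, 16, 24 or 40 per arm). Normal-approximation power is then about 14%, 25%, 35% and 54%. Fisher's test has less: under 0.1%, 1.7%, 8.5% and 20.6%. Power would be higher if failures concentrate in that stratum.

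**The case against.** The error is conservative. It creates no bias and no excess of false positives. Stratified allocation still makes the estimate itself less variable; what is missing is credit for this in the reported standard error. The loss depends on an R² that nobody has stated, and at 0.02–0.05 it is only 1–3% of the standard error. The trial is sized on first-attempt success, where the gain is often nil. All of this stands and sets the size of the point.

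Three stronger readings are tempting, and the document does not support them.

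- A reader might infer that every planned analysis ignores the strata. The regressions for predictors of failure and of difficult intubation name no covariates and could include the ADA score. The omission is certain only for the stated chi-square/Fisher and ANOVA comparisons.
- A reader might infer that power is simply lost on the endpoint that sizes the trial. A gain of 3 points or more over Fisher appears only if about 80% or more of failures fall in a 20–30% difficult stratum. With equal strata there is none, and if the articulating stylet also fails occasionally the change can go either way.
- A reader might infer that the hypothesis for difficult airways will never be tested. A condensed article cannot show that, since a by-stratum analysis may sit in a document not at hand. The Background sentence can also be read as describing the mixed population, and it concerns time, haemodynamics and trauma rather than first-attempt success.

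It might also be said that model terms belong in the analysis plan. That answers a gap, but here the tests are named, and as named they leave out the allocation factor.

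**Conclusion.** The point holds in limited form. The between-group tests stated for the three primary endpoints omit the factor used to allocate patients.

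- **Times and IDS:** conservative if the stratum is prognostic, by the amounts in step 2 of the working. These rest on the assumed R² range of 0.02 to 0.30, and the 1–12 points of power are on the ordinary-formula footing.
- **First-attempt success:** nothing to gain at the design rates if failures are evenly spread or the strata are equal; about 2–6 points over pooled Fisher if 70–90% of failures fall in a 20–30% difficult stratum.
- **Both-anatomies hypothesis:** no by-stratum comparison is stated, and the pooled tests cannot carry a claim about difficult airways.

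None of this threatens the validity of a positive result. It is worth correcting because the correction is nearly free.

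**What to change.** Amend Statistical considerations as follows:

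- Times and IDS: add the ADA stratum as a factor in the ANOVA or linear model, and report the adjusted difference with its 95% confidence interval.
- First-attempt success: use a CMH test stratified by ADA level, in its exact form if failures are sparse, with a stratum-weighted risk difference. Ordinary adjusted logistic regression is not a safe substitute, because 100% success in one arm produces separation.
- By stratum: report stratum-specific effects and the treatment-by-stratum interaction as estimates with confidence intervals. State that the difficult stratum alone has low power at the design difference, and limit any claim about difficult airways to what those intervals show.

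The cost is analysis wording only. The ADA stratum is known for every patient before allocation, and neither the sample size nor data collection changes. Trial status reports 11 patients recruited at submission, so at that stage the change could still be prespecified.
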